# Pulmonary Hypertension: Intensification and Personalization of Combination Rx (PHoenix): A phase IV randomized trial for the evaluation of dose‐response and clinical efficacy of riociguat and selexipag using implanted technologies

**DOI:** 10.1002/pul2.12337

**Published:** 2024-03-17

**Keywords:** oral prostacyclin‐receptor agonist, remote monitoring, soluble guanylate‐cyclase stimulator, targeted therapy

## Abstract

Approved therapies for the treatment of patients with pulmonary arterial hypertension (PAH) mediate pulmonary vascular vasodilatation by targeting distinct biological pathways. International guidelines recommend that patients with an inadequate response to dual therapy with a phosphodiesterase type‐5 inhibitor (PDE5i) and endothelin receptor antagonist (ERA), are recommended to either intensify oral therapy by adding a selective prostacyclin receptor (IP) agonist (selexipag), or switching from PDE5i to a soluble guanylate‐cyclase stimulator (sGCS; riociguat). The clinical equipoise between these therapeutic choices provides the opportunity for evaluation of individualized therapeutic effects. Traditionally, invasive/hospital‐based investigations are required to comprehensively assess disease severity and demonstrate treatment benefits. Regulatory‐approved, minimally invasive monitors enable equivalent measurements to be obtained while patients are at home. In this 2 × 2 randomized crossover trial, patients with PAH established on guideline‐recommended dual therapy and implanted with CardioMEMS™ (a wireless pulmonary artery sensor) and ConfirmRx™ (an insertable cardiac rhythm monitor), will receive ERA + sGCS, or PDEi + ERA + IP agonist. The study will evaluate clinical efficacy via established clinical investigations and remote monitoring technologies, with remote data relayed through regulatory‐approved online clinical portals. The primary aim will be the change in right ventricular systolic volume measured by magnetic resonance imaging (MRI) from baseline to maximal tolerated dose with each therapy. Using data from MRI and other outcomes, including hemodynamics, physical activity, physiological measurements, quality of life, and side effect reporting, we will determine whether remote technology facilitates early evaluation of clinical efficacy, and investigate intra‐patient efficacy of the two treatment approaches.

## INTRODUCTION

Pulmonary arterial hypertension (PAH) represents a spectrum of disease that may be idiopathic or associated with genetic mutations, connective tissue disease, congenital heart disease, or drug/toxin exposure.^1^ At a cellular level, disease is driven by remodeling and constriction of the small pulmonary arteries, which can lead to right‐sided heart failure and premature death.^1^ Currently available targeted therapies for this progressive disease mediate pulmonary vascular vasodilatation by acting on one of three pathways—the endothelin pathway via endothelin receptor antagonists (ERA), the nitric oxide (NO) pathway via phosphodiesterase type‐5 inhibitors (PDE5i) or soluble guanylate cyclase stimulators (sGCS), or the prostacyclin pathways via prostacyclin analogs and prostacyclin receptor (IP) agonists.^1^, ^2^ Despite the range of therapies available, drug choice is empirical and based on a hospital‐based risk stratification that matches the number of vasodilator agents to disease severity.^2^

Approved therapies targeting the endothelin, NO, or prostacyclin pathways have been shown to provide improvements in pulmonary vascular hemodynamics and 6‐min walk test (6MWT) in phase 2/3 studies.^1^, ^3^, ^4^, ^5^, ^6^, ^7^ Evidence shows that time to clinical worsening is further improved in patients established on dual therapy with an ERA and a PDE5i, when compared with monotherapy with either agent.^2^, ^8^ In line with European guidelines,^2^ for patients established on dual oral therapy (PDE5i/ERA) with an inadequate treatment response, NHS England's National Commissioning Policy permits the addition of the selective IP receptor agonist selexipag, or switching of PDE5i for the sGCS riociguat.^9^, ^10^ There is clinical equipoise between these two approaches (i.e., triple therapy with selexipag + PDE5i + ERA and dual therapy with riociguat + ERA).

Selexipag, an IP receptor agonist, improves the time‐to‐clinical‐worsening in patients on a range of background therapy regimens (including patients on no therapy [20.4%]; ERA or PDE5i monotherapy [47.1%]; and ERA/PDE5i dual therapy [32.5%]).^4^ However, data suggest that initiating triple therapy (PDE5i/ERA/IP receptor agonist) compared with dual therapy (PDE5i/ERA) in newly diagnosed treatment naïve patients offers no significant improvement in snapshot hemodynamic measurements or exercise capacity.^11^ Additionally, switching PDE5i for another drug targeting the NO pathway (riociguat, an sGCS) improves disease severity as assessed by World Health Organization (WHO) functional class and 6MWT distance, and reduces clinical worsening events compared with continuing PDE5i therapy.^12^ In all regulatory approval studies, significant side effects and therapeutic non‐adherence were observed.^4^, ^6^, ^12^, ^13^, ^14^, ^15^, ^16^, ^17^, ^18^

In clinical practice, response to therapy and/or assessment of disease progression is made by assessing pressure and flow during invasive right heart catheterization, by monitoring the downstream effect on right heart structure and function, and by evaluating exercise capacity. European Society of Cardiology (ESC) guidelines recommend invasive assessment of cardiopulmonary hemodynamics for disease diagnosis, assessment of severity, and to inform treatment decisions (therapeutic change and transplant).^2^ Other recommended means of guiding treatment decisions include regular measurement of exercise capacity by 6MWT, disease‐specific risk scoring, assessment of right heart strain by N‐terminal pro‐brain natriuretic peptide (NT‐proBNP), and/or noninvasive imaging, with magnetic resonance imaging (MRI) acknowledged to be more accurate than echocardiography.^2^

The currently established standard for phase 2 studies of PAH therapies includes the assessment of invasive hemodynamics and the 6MWT.^1^ However, recent studies have demonstrated that noninvasive endpoints, such as right ventricular ejection fraction (RVEF) and right ventricular stroke volume (RVSV) measured by MRI, are repeatable, and detect treatment change in a manner similar to invasive catheterization and NTpro‐BNP, thereby establishing MRI as a robust, objective, noninvasive assessment of treatment response in patients with PAH.^19^, ^20^

Despite these advances, there remains a need for invasive/hospital‐based investigations to assess disease severity and demonstrate therapeutic benefit, and there are currently no means for early assessment of clinical efficacy in patients with PAH. This limits experimental medicine and drug development studies and prevents personalized medicine in clinical practice. Development of innovative approaches to monitor PAH outcomes is essential for a number of reasons including poor prognosis among patients with PAH, reduced quality of life, side effect profile of approved therapies, nonuniform drug response among patients, high cost of PAH‐specific therapies (£5–120k/medication/patient/year), and emerging therapies with proven benefit in preclinical studies.^9^, ^19^, ^20^, ^21^, ^22^

In patients with PAH, cardiopulmonary hemodynamics are closely associated with clinical outcomes,^7^ and are affected by both diseases worsening and increase or withdrawal of therapy.^23^, ^24^ The development of minimally invasive technology that provides remote, daily measurement of cardiopulmonary hemodynamic parameters and physical activity may provide more comprehensive coverage of the effects of treatment on patients' daily functioning, allowing insight into the intervening periods between scheduled hospital visits.^25^ Remote monitoring may provide benefits to both patients and care teams by allowing remote monitoring of efficacy following a treatment change. This may permit a personalized management approach, with the care team able to optimize therapy remotely—balancing therapeutic efficacy with side effects in each individual patient. Indeed, in patients with heart failure, remote, hemodynamic‐guided therapy has been demonstrated to reduce heart failure hospitalization,^26^, ^27^ and these studies have led to regulatory approval of pulmonary artery pressure (PAP) monitors. Furthermore, studies of patients with PAH implanted with a PAP monitor and an insertable cardiac monitor (ICM) demonstrated that clinically indicated therapeutic changes altered physiological parameters associated with mortality, indicating that early, remote assessment of clinical efficacy may be achieved using these devices.^28^

CardioMEMS™ HF System (Abbott) is a wireless, PAP monitor implanted at the time of right heart catheterization to provide remote measurement of cardiopulmonary hemodynamics. CardioMEMS is approved for routine clinical practice in the USA and Europe, and to date over 30,000 of these monitors have been implanted. The Confirm Rx™ ICM (Abbott) is a minimally invasive regulatory‐approved cardiac monitor, implanted in a clinical setting for patients who experience unexplained symptoms, such as dizziness; palpitations, chest pain, syncope, shortness of breath, as well as for patients who are at risk for cardiac arrhythmias. Over 40,000 Confirm RX™ have been implanted and the device is in routine clinical use in the United Kingdom.

Here, we detail the protocol for a study in which patients with PAH, established on guideline‐recommended dual oral therapy and evaluated as intermediate‐low risk,^29^ will be implanted with CardioMEMS and ICM devices. Following implantation, patients will enter a 2 × 2 crossover study in which PDEi will be replaced with sGCS (ERA + sGCS), or an IP receptor agonist will be added to PDEi and ERA (PDEi + ERA + IP receptor agonist). Data obtained from remote monitoring will be compared with that from established clinical investigations undertaken at baseline and maximal therapy on each drug. The crossover design of this study, which will incorporate structured up‐titration of these drugs, is aimed at evaluating the capacity of implantable technology for early evaluation of the clinical efficacy of these drugs. A crossover study is a logical study designed to investigate the intra‐patient efficacy of these treatment options and increase the power to detect clinical efficacy. Additionally, the study will provide insight into the capacity of remote monitoring technology to facilitate trials that are not currently possible due to the requirement for repeated, hospital‐based invasive/imaging procedures.

## METHODS

### Study design

This open‐label, phase 4, multicentre, randomized 2 × 2 crossover study (NCT05825417) in patients with PAH established on dual therapy (PDE5i/ERA) will evaluate the effects via clinical investigations, patient‐reported outcomes and remote cardiac monitoring of two therapeutic strategies—adding an oral drug targeting the prostacyclin pathway (selexipag; PDEi + ERA + IP receptor agonist) and switching of PDE5i to an sGCS (riociguat; ERA + sGCS). Using the 2 × 2 crossover trial design, patients will receive both therapies, but the sequence will be randomly assigned with washout phases between therapies, and assessments of response to each therapy to be performed.^30^ The study protocol was approved by the NHS Health Research Authority (IRAS PROJECT ID 325120, REC Reference 23/NE/0067). A tabulated summary of all visits and assessments is provided in Supporting Information: Table S1.

### Objectives and endpoints

The main aims of this study will be to assess the individual difference in effect between treatment escalation with selexipag (PDEi + ERA + IP receptor agonist) or riociguat (riociguat; ERA + sGCS) on RV stroke volume (flow) as measured by cardiac MRI in patients with intermediate‐low risk PAH, and to determine whether remote monitoring devices can be used to provide an early assessment of clinical efficacy of drug therapies for PAH.

The primary endpoint will be change in RVSV (flow) measured by MRI from baseline to 12 weeks for each therapeutic strategy. Change in RVSV provides a robust, objective assessment of clinical efficacy and will represent a clinically meaningful change in physiology.^31^ ESC guidelines recommend follow‐up at 3–6 months after a change in therapy. Titration protocols mimic standard clinical care and expected time‐to‐improvement.^2^

Secondary endpoints for each therapeutic strategy include change from baseline to 12 weeks in hemodynamics (total peripheral resistance [TPR], mean pulmonary artery pressure [mPAP], cardiac output [CO], cardiac index, stroke volume [SV], heart rate [HR]), 6MWT, NTpro‐BNP, MRI parameters (RVEF, right ventricular end‐systolic volume [RVESV], right ventricular end‐diastolic volume [RVEDV], RVSV (volume), left ventricular ejection fraction [LVEF], left ventricular end‐systolic volume [LVESV], left ventricular end‐diastolic volume [LVEDV], and LVSV flow), quality of life (EmPHasis‐10), medication compliance (PHoenix PRO) and side effects, depression and anxiety symptoms (Generalized Anxiety Disorder‐[GAD]‐2/7 and Patient Health Questionnaire [PHQ]‐2/9), WHO functional class, and activity levels as measured with a Garmin Venu2 smartwatch. A full list of outcome measures is provided in Table 1.

**Table 1 pul212337-tbl-0001:** Outcome measures.

	Hospital‐based measures	Remotely monitored measures
Primary outcomes	Change in RVSV (flow) measured by MRI	
Secondary outcomes	Haemodynamics: TPR mPAP CO Cardiac index SV HR MRI parameters: RVEF RVESV RVEDV RVSV (volume) LVEF LVESV LVEDV LVSV flow Other parameters: 6MWT NTpro‐BNP WHO functional class Quality of life (EmPHasis‐10) Depression and anxiety symptoms (GAD‐2/7 and PHQ‐2/9) Medication compliance (PHoenix PRO questionnaire) Side effects	Confirm Rx: HR HR variability Cardiac rhythm Thoracic impedance Respiratory rate CardioMEMS: mPAP CO SV Smartwatch (Garmin Venu2): Physical activity Physiological measurements (TPR, mPAP, CO, cardiac index, SV, and HR) Phone apps: PRO (Phoenix remote questionnaire) Medication compliance (myCardioMems app) 6MWT

Abbreviations: 6MWT, 6‐min walk test; CO, cardiac output; GAD, Generalized Anxiety Disorder; HR, heart rate; LVEF, left ventricular ejection fraction; LVEDV, left ventricular end‐diastolic volume; LVESV, left ventricular end‐systolic volume; mPAP, mean pulmonary artery pressure; PHQ, Patient Health Questionnaire; PRO, patient‐reported outcome; RVEDV, right ventricular end‐diastolic volume; RVESV, right ventricular end‐systolic volume; RVSV, right ventricular stroke volume; SV, stroke volume; TPR, total peripheral resistance.

Established clinical study endpoint measures at maximal therapy will be compared to changes in remotely monitored parameters measured at 4 and 8 weeks to determine if the implanted devices can detect structured changes in the clinical therapy, thereby facilitating early assessment of clinical efficacy. Remotely monitored parameters to be correlated with maximal therapy assessments, measured as absolute change from baseline and area under the curve to 4 and 8 weeks on each therapy, include hemodynamics (mPAP, CO, cardiac index, TPR, day HR, night HR, and HR reserve), activity (minutes per day), 6MWT, and PRO.

The analysis will also be performed to determine if changes in established and remotely monitored parameters (primary and secondary endpoints) can detect individual patient‐level therapy effects, thereby determining the utility of remote monitoring for personalized treatment plans.

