### Clinical assessments

Patients will undergo clinical assessments at baseline before receiving study drug treatment, and at Weeks 12 and 27 of the treatment schedule (Figure 1); these will include hemodynamics, 6MWT, MRI, and NT‐proBNP assessments.

MRI analysis will be provided by a study‐appointed core lab using certified clinicians; scans will be deidentified and analyzed in random order independent of patient and time point. Analysis of primary and secondary endpoints will be undertaken in a blinded manner by an independent statistical team in accordance with a pre‐specified statistical analysis plan.

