### Statistical analyses

#### Sample size calculation

The sample size was chosen to ensure adequate power to detect differences in the clinical efficacy of the two treatment approaches in population‐level analyses and to have adequate power to evaluate the ability of implantable/remote technology to provide early evaluation of such clinical efficacy. For comparing the clinical efficacy of the two treatment approaches, we have used published RVSV data reporting a minimal clinically important difference of 12 mL and within‐patient standard deviation (SD) of 16.5 mL.^38^ The current study will be powered using a standardized effect (SE) of 12/16.5 = 0.73. Assuming 1:1 randomization of the participants to the two treatment sequences, 40 participants will provide 90% power in the population‐level clinical efficacy analysis for a 5% two‐sided type‐I error rate, with SE of 0.73. This is below the SE previously reported for the pulmonary vascular resistance (PVR; SE = 353.4/219.0 = 1.61),^3^ and the RVEF (SE = 9.12/7.39 = 1.23)^20^ and comparable to that observed for the 6MWT (SE = 36.0/46.7 = 0.77).^6^ Therefore, the study will be well‐powered for population‐level analyses of these additional important outcomes.

The sample size of 40 also provides good power for assessing whether changes in remote physiological measures from baseline to 4 and 8 weeks (mPAP, CO, HR, and heart rhythm) are correlated with changes in clinical measures from baseline to 12 weeks. The sample size of 40 patients provides 90% power, at a two‐sided 5% type‐I error rate, for correlations greater than 0.5, which would represent those of clinical interest.

The study is not powered for formal mediation analysis, so this will be considered exploratory. No formal multiple‐testing correction will be applied.

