#### Statistical analysis plan

All statistical analysis plans (SAPs) will be drafted early in the study and finalized before the analysis of unblinded data.

The primary clinical efficacy analysis will use a linear mixed effects model with the dependent variable being the change in RVSV (flow) from baseline to 12 weeks. “Baseline” and “12 weeks” refer to the time points within each treatment period. Each participant will contribute up to two observations if they complete both treatment periods. A random effect for each participant will be included together with the within‐treatment period baseline RVSV (flow) measurement, a fixed period effect, and treatment (selexipag or riociguat) allocated during the treatment period. This model will be used to estimate the mean difference between the two treatment approaches (ERA + sGCS and PDEi + ERA + IP receptor agonist), together with a 95% confidence interval and a *p* value using a Wald test.

Similar methods will be applied to the analysis of secondary efficacy outcomes. Treatment effect heterogeneity between subgroups will be assessed by including treatment‐by‐subgroup interaction terms in regression models. Main analyses will use complete data only, but multiple imputation will be used for missing data in sensitivity analyses. No adjustments will be made for multiple statistical tests. All efficacy analyses will follow the intention to treat principle (i.e., analysis according to randomized treatment, regardless of treatment compliance). Safety data (adverse events and side effects) will be summarized in relation to treatment being received at the onset of the event, and the study period (pretreatment period 1, treatment period 1, washout period, treatment period 2, posttreatment period 2); no formal statistical comparisons will be applied.

To analyze whether changes in RVSV (flow) may be explained by remotely monitored physiological parameters, we will test whether there is a significant correlation between the change between baseline and Week 4/Week 8 physiological parameters and the change between baseline and Week 12 RVSV (flow) outcome. We will also adopt a mediation analysis approach to investigate what proportion of the change between baseline and Week 12 RVSV (flow) is explained by the change between baseline and Week 4/Week 8 physiological parameters using the mediation package in R. Secondary endpoints will be analyzed using appropriate regression models.

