## DISCUSSION

Patients with PAH receiving dual combination treatment (PDE5i + ERA) who are stratified as being at intermediate‐low risk^39^ are recommended to intensify therapy via the addition of the IP receptor agonist, selexipag, or to switch from a PDE5i to the sGCS, riociguat.^9^, ^10^, ^29^ There is clinical equipoise between triple therapy with selexipag + PDE5i + ERA and dual therapy with riociguat + ERA. Conducting head‐to‐head clinical trials to compare treatment strategies in patients with PAH is challenging due to the current necessity for repeated, hospital‐based invasive/imaging procedures to evaluate treatment efficacy. Remote hemodynamic and cardiac monitoring may provide a means for early, minimally invasive evaluation of clinical efficacy and early identification of clinical worsening in patients with PAH, which may facilitate study designs evaluating dose–response, time‐to‐effect and head‐to‐head comparison. This study is designed to assess the individualized effect of selexipag and riociguat on RV stroke volume as measured by cardiac MRI, and to determine whether remote monitoring devices can be used to provide an early assessment of the clinical efficacy of drug therapies for PAH. This hybrid drug‐device regulatory‐approved design represents the first evaluation of an sGCS and IP agonist.

This blinded analysis of objective MRI measures provides an efficient, robust, and effective clinical study structure. As the primary endpoint is objective with blinded analysis, patients and clinicians will not be blinded to the sequence of drug allocation and up‐titration.

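### The individual drug difference in MRI stroke volume is named as a main aim, but a 2 × 2 crossover with one on-treatment MRI per drug identifies only the mean within-patient difference

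*Protocol article*

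**What the plan says.** Three places in the protocol article set an aim at the level of the single patient.

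- Objectives and endpoints, opening sentence: "The main aims of this study will be to assess the individual difference in effect between treatment escalation with selexipag" or riociguat, the measure being RV stroke volume (flow) on cardiac MRI.
- Objectives and endpoints, last paragraph: an analysis is to establish whether changes in the established and remote parameters, expressly including the primary endpoint, "can detect individual patient‐level therapy effects, thereby determining the utility of remote monitoring for personalized treatment plans".
- Discussion: "This study is designed to assess the individualized effect of selexipag and riociguat on RV stroke volume as measured by cardiac MRI".

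The design and analysis sections describe something narrower.

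- Study design: "patients will receive both therapies, but the sequence will be randomly assigned with washout phases between therapies". Each drug is given in one period.
- Clinical assessments, which include MRI: "Patients will undergo clinical assessments at baseline before receiving study drug treatment, and at Weeks 12 and 27 of the treatment schedule". That is one on-treatment scan per drug.
- Statistical analysis plan section: "Each participant will contribute up to two observations if they complete both treatment periods". The model is built as follows: "A random effect for each participant will be included together with the within‐treatment period baseline RVSV (flow) measurement", plus fixed effects for period and treatment. Its output is a mean difference between the two strategies.
- Sample size calculation: power is claimed for the population-level comparison, from a 12 mL important difference and a "within‐patient standard deviation (SD) of 16.5 mL", and for correlations between remote and clinical measures. No power or precision is given for an individual-level result.

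**The concern.** A patient's observed drug difference is the sum of that patient's true difference and whatever else changed between the two assessment occasions. To separate the two, the same patient must be observed on the same drug in more than one period. A 2 × 2 crossover has no such repetition, so patient-by-drug interaction is fully confounded with within-patient error. This follows from the stated design, and no choice of model in an unseen analysis plan can remove it.

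At stake is what the trial may conclude about personalised treatment. A wide spread of individual MRI differences would be expected even if the two strategies differed by the same amount in every patient. The spread alone cannot show that some patients do better on one drug and some on the other.

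**Working it through.** **Inputs.** From the Sample size calculation: important difference 12 mL, within-patient SD 16.5 mL, N = 40, 90% power, two-sided 5%. From Study design, Clinical assessments and the Statistical analysis plan section: one period and one on-treatment MRI per drug, and at most two observations per patient.

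**Step 1: reproduce the plan's sample size, to see what 16.5 mL means.** For a 2 × 2 crossover with per-occasion within-patient SD σ, the within-patient drug difference has variance 2σ², and

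N = 2 × [σ × (1.960 + 1.282) / δ]² = 2 × [16.5 × 3.242 / 12]² = 39.7, rounded up to 40.

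Power at N = 40 is 90.2% by the normal approximation (88.7% by noncentral t with 38 df). If 16.5 mL were the SD of the paired difference, N would be 19.9, so 20. Reading 16.5 mL as the per-occasion SD is therefore what gives the stated 40. The calculation is sound, and it concerns the mean difference.

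**Step 2: what the data can identify.** Let D be one patient's observed drug difference, τ the SD of true individual differences across patients, and σ the within-patient occasion-to-occasion SD:

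Var(D) = τ² + 2σ².

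With one on-treatment occasion per drug, only the sum can be estimated. Each row below gives the same SD of D, 16.5 × √2 = 23.3 mL. The limits are 1.96 × √2 × σ.

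| τ (mL) | σ (mL) | SD of D (mL) | 95% noise limits for one patient (mL) |
|---|---|---|---|
| 0 | 16.5 | 23.3 | ±45.7 |
| 6 | 15.9 | 23.3 | ±44 |
| 12 | 14.2 | 23.3 | ±39 |
| 16.5 | 11.7 | 23.3 | ±32 |

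The planned data cannot tell these rows apart. In the first, every patient has the same true difference. In the last, true differences vary widely.

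**Step 3: size for one patient, under two readings of 16.5 mL, each treating all of it as noise.**

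| Quantity | Per-occasion SD (reproduces N = 40) | SD of the paired difference |
|---|---|---|
| Noise SD of D | 16.5 × √2 = 23.3 mL | 16.5 mL |
| 95% limits | ±1.96 × 23.3 = ±45.7 mL | ±1.96 × 16.5 = ±32.3 mL |
| Chance that D is at least 12 mL in either direction when the true difference is 0: 2 × [1 − Φ(12/SD)] | 0.61 (about 24 of 40) | 0.47 (about 19 of 40) |
| Chance of the wrong sign when the true difference is 12 mL: Φ(−12/SD) | 0.30 | 0.23 |

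**Step 4: would repetition help?** With k independent periods per drug, the noise SD of a patient's mean difference is 23.3/√k. For k = 2 it is 16.5 mL (±32.3 mL), and τ becomes estimable. Limits of ±12 mL would need k = (45.7/12)² = 14.5, so about 15. This shows the scale of the problem and is not a proposal.

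**The case against.** The strongest reply is that individual difference means no more than a comparison made within each patient and then averaged. The design supports that, and the primary model and sample size already target the mean. The point holds for the analysis, but this reading does not fit the last paragraph of the Objectives section, which asks about effects at the level of single patients and includes the primary endpoint among the measures tested. The wording needs correcting even if the sponsor intended the milder sense.

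Second, that paragraph poses a question: whether such effects can be detected, with the usefulness of remote monitoring as its purpose. This is fair. A reader might infer that the trial will label patients as responders or assign them a preferred drug from their MRI values. The article contains no such rule, and the individual-level method is not described.

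Third, 16.5 mL comes from a cited source that is not at hand, and it is not described as a scan–rescan SD. This also stands. The variation at issue is all occasion-to-occasion variation within a patient, not MRI repeatability alone. A reader might conclude that individual MRI differences will be mostly noise. That is not shown, because the noise share is exactly what the design leaves unknown, and the limits narrow if part of the SD is true interaction.

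Fourth, the primary model refers to a within-period baseline, so a second baseline scan may exist. It would not replicate the on-treatment response. The planned subgroup interactions concern groups, not individuals.

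Finally, the remote readings are daily, and it is tempting to move the individual-level claim to them. Daily values do reduce measurement noise, but each drug still has only one period. Patient-by-drug effects in the remote data stay confounded with patient-by-period variation, and intervals built from day-to-day scatter alone would be too narrow.

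**Conclusion.** The concern holds in this form: the article names individual drug differences in MRI stroke volume as an aim, and the design can deliver only their mean. The confounding depends on no numerical assumption. Its size does. On the reading that reproduces N = 40, with all of 16.5 mL taken as noise, the limits for one patient are about ±46 mL, nearly four times the 12 mL important difference (45.7/12 = 3.8), and 61% of patients would reach 12 mL with no true difference. On the paired-difference reading the figures are about ±32 mL and 47%. Across the splits of the SD shown in the working, the limits run from about ±46 down to ±32 mL, so even the narrowest is more than twice 12 mL.

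A reader might take this as a flaw in the primary analysis. It is not: the mean comparison, its sample size and its test are unaffected. The fault lies in a stated aim that the design cannot answer, and it should be corrected before results are interpreted.

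**What to change.** 1. In both places in Objectives and endpoints, and in the Discussion, restate the MRI aim as the mean within-patient difference between the two strategies.
2. If individual MRI differences are shown, label them exploratory. Give an error range with its assumption (which SD, what it represents, and that it is treated as noise), and draw no responder or preferred-drug conclusion.
3. Apply the same caution to individual estimates from the remote readings: call them exploratory, and state that with one period per drug they cannot be separated from patient-by-period variation.

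The cost is wording and labelling only, with no added patients, visits or scans. The downside is a less ambitious claim about personalisation.
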